## Abstract

**Background:**

Patients with gaps in health insurance coverage often defer or forgo cancer prevention services. These delays in cancer detection and diagnoses lead to higher rates of morbidity and mortality and increased costs. Recent advances in health information technology (HIT) create new opportunities to enhance insurance support services that reduce coverage gaps through automated processes applied in healthcare settings. This study will assess the implementation of insurance support HIT tools and their effectiveness at improving patients’ insurance coverage continuity and cancer screening rates.

**Methods/design:**

This study uses a hybrid cluster-randomized design—a combined effectiveness and implementation trial—in community health centers (CHCs) in the USA. Eligible CHC clinic sites will be randomly assigned to one of two groups in the trial’s implementation component: tools + basic training (Arm I) and tools + enhanced training + facilitation (Arm II). A propensity score-matched control group of clinics will be selected to assess the tools’ effectiveness. Quantitative analyses of the tools’ impact will use electronic health record and Medicaid data to assess effectiveness. Qualitative data will be collected to evaluate the implementation process, understand how the HIT tools are being used, and identify facilitators and barriers to their implementation and use.

**Discussion:**

This study will test the effectiveness of HIT tools to enhance insurance support in CHCs and will compare strategies for facilitating their implementation in “real-world” practice settings. Findings will inform further development and, if indicated, more widespread implementation of insurance support HIT tools.

**Trial registration:**

Clinical trial NTC02355262

## Background

Cancer morbidity and mortality can be greatly reduced through screening and prevention; however, not all patients have access to regular cancer prevention services. In the USA, uninsured populations are much less likely to receive these evidence-based services as recommended, compared to those with insurance coverage [1–8]. Further, when health insurance coverage gaps occur, patients often delay or forgo cancer prevention services [9–13]. These delays in cancer detection and diagnoses lead to higher rates of disease incidence and mortality and increased healthcare costs [2, 14–22]. Patients who regain health insurance coverage are often able to catch up on missed prevention services [9–13]. Thus, interventions that optimize and stabilize health insurance coverage could substantially improve rates of receipt of timely cancer preventive care.

Community health centers (CHCs) are well-positioned to provide such health insurance support because many of their patients are uninsured or experience frequent coverage gaps [23, 24]. Recent advances in health information technology (HIT) create new opportunities for enhancing insurance support services in CHCs and other healthcare settings through automated processes. Since the passage of the Affordable Care Act (ACA) in 2010, there are new insurance programs (i.e., Medicaid expansions) available for socioeconomically vulnerable patients [25]. This confluence of factors presents a window of opportunity to develop, test, and implement health insurance support technologies.

### Health insurance support HIT tools

Most healthcare institutions collect information about patients’ insurance coverage. These data are documented in the electronic health record (EHR) but then are often used exclusively for billing purposes. While many CHCs already engage in health insurance support, few have an automated way to use patients’ health insurance data to identify, track, or communicate with patients about their health insurance status. We built insurance support HIT tools that incorporated information already in the EHR, augmented by the collection of a few additional data elements. These insurance support HIT tools were modeled on those proven effective for chronic disease management such as a computer reminder system for colorectal cancer screening [26–28]. The tools include a panel management/data aggregator system, which identifies patients who may be eligible for Medicaid coverage but are not yet insured or who may be nearing coverage expiration.

In recent pilot studies, we showed that these insurance support HIT tools can be integrated into clinic workflows in several ways [29–31]. The tools can provide “pop-up” alerts that appear at check-in or while scheduling an appointment. The tools also create registry lists of patients who are uninsured or may be nearing insurance expiration dates. These registries provide clinic staff with information about patients to contact and offer insurance enrollment support. Registries also can be used to support automatic messages (e.g., e-mail, voicemail, texts, after-visit communications) to remind patients about upcoming insurance re-enrollment dates and provide them with resources.

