#### Pre-implementation phase

We will first assess baseline rates of insurance coverage, cancer screening, and general recommended preventive care across all study arms and the matched controls. We will also assess rates of these outcomes across the total OCHIN population to compare to the recruited clinics. Additional analyses including patients from all CHCs in OCHIN will be conducted to assess the impact of recent policy changes on insurance coverage and cancer preventive care. Data for these analyses will be extracted from the OCHIN EHR and will include demographic information (i.e., age, federal poverty level, race/ethnicity, language spoken), insurance coverage dates and types, as well as cancer screenings (e.g., fecal occult blood test (FOBT) orders, colonoscopy and mammography referrals, and pap smear receipt), immunizations (e.g., human papillomavirus (HPV) vaccination), cancer-related health behavior assessment and counseling (e.g., smoking screening and intervention and obesity screening and intervention), and receipt of general recommended preventive care (e.g., blood pressure, glucose, and lipid assessments). This information will be extracted using standardized codes for diagnoses, labs, medications, procedures, and referrals, and electronically collected vital signs and social history (e.g., smoking status) from visits. As seen in Table 2, we will define receipt of cancer screenings and prevention based on services with an A–B rating from the US Preventive Services Task Force and recommendation from the Advisory Committee on Immunization Practices [45, 46]. Our EHR dataset will also contain additional information about the use of health services such as encounter information, provider data, clinic location, reason for visit, level of service, and type and number of visits.

**Table 2 Tab2:** Description of outcome measures

Dependent variable	Description/measure for preventive care
Insurance coverage	Covered at visit (yes, no); all visits covered vs. not covered; percent of visits covered
Insurance continuity	Months covered by Medicaid; percentage of time covered by Medicaid
Recommended preventive care services (NQF)	Breast cancer screening^a^ (0031), NCQA; currently used by MU1, HEDIS®, and MACS
	Cervical cancer screening^a^ (0032), NCQA; currently used by MU1, HEDIS®, and MACS
	Colorectal cancer screening^a^ (0034); MU1, HEDIS®

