This protocol has several limitations. First, a participant site could withdraw from the study; however, the large number (>300) of OCHIN member CHCs could provide substitute sites. Second, as with any study conducted in “real-world” settings, unobserved changes will undoubtedly occur over time in a non-random fashion within the study environments (e.g., community health insurance outreach efforts). We acknowledge that these unexpected occurrences may make it difficult to isolate the effect of the health insurance support HIT tools and the implementation support strategies in this pragmatic trial. To address this, our approach uses both clinic- and individual-level comparisons. Further, the implementation component of this trial is strengthened by the use of a two-arm cluster-randomized design, and the tool effectiveness component uses a propensity score-matched control group of clinics to adjust for temporal trend. Third, while EHR data sources are not developed for research purposes, we have conducted multiple validation studies and have successfully built research datasets in the past [31–69]. Finally, as with most implementation research, there are questions about sustainability. Conducting this work in partnership with OCHIN positions us to sustain the aspects of the insurance support HIT tools proven effective. OCHIN is committed to maintaining the tools and will also enable rapid dissemination to more CHCs.

Despite these limitations, this study has great potential impact, given the central role played by CHCs in providing health care to vulnerable populations and the expansion of both CHCs and public health insurance coverage for adults as supported by the American Recovery and Reinvestment Act and the ACA [70]. Indeed, as health insurance expansions continue, it becomes increasingly important to know about effective methods for connecting patients to coverage. The proposed study will contribute to this knowledge gap. We believe our findings will have broad relevance to public health and healthcare reform efforts. We will work with our community partners and state policymakers to widely distribute findings and plan for widespread dissemination of the insurance support HIT tools, if proven effective. Further, the insurance support HIT tools have the potential to facilitate access to a wide range of recommended healthcare services beyond cancer screening and prevention.

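### The tools work inside the EHR that supplies the insurance data, so a change in recording at tool clinics could bias EHR visit coverage in either direction, and difference-in-differences would not remove it

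*Protocol article*

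**What the plan says.** The Background section on the HIT tools describes the intervention as part of the EHR: "We built insurance support HIT tools that incorporated information already in the EHR, augmented by the collection of a few additional data elements". It adds: "The tools can provide “pop-up” alerts that appear at check-in or while scheduling an appointment". And: "The tools also create registry lists of patients who are uninsured or may be nearing insurance expiration dates".

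Under Pre-implementation phase the data source is given as follows: "Data for these analyses will be extracted from the OCHIN EHR and will include demographic information". The list that follows includes "insurance coverage dates and types". Table 2 has two insurance outcomes. Coverage is scored at visits; continuity is the number of months, or the share of time, on Medicaid. The Reach measure for the implementation component also uses insured visits.

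The abstract says that the quantitative analyses "will use electronic health record and Medicaid data to assess effectiveness". The outcome and analysis sections do not say which insurance outcome uses the Medicaid data. On the quality of EHR data, the limitations say: "we have conducted multiple validation studies and have successfully built research datasets in the past".

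Control clinics do not have the tools (Study measures for the effectiveness component). The comparison is a difference-in-differences over 18 months before and 18 months after the intervention. Arm I is compared with Arm II in the same way.

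**The concern.** The intervention sits inside the instrument that measures one of its outcomes. Alerts can appear at check-in, which is part of the visit at which coverage is scored. The registries pick out patients by their recorded insurance status or expiry date. Staff who act on an alert or a list may learn that the record is wrong and correct it. Control staff get no such prompt. Arm II staff get more help in using the tools than Arm I staff, and the authors hypothesize higher uptake there.

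If this happens, recorded coverage at tool clinics changes for a reason other than a change in true coverage. Insurance coverage is the first study objective and the proposed route to better screening. A difference in EHR visit coverage, between tool and control clinics or between the arms, could then not be cleanly separated from a difference in record-keeping. Randomization of organizations to Arm I or Arm II does not protect against ascertainment that differs by arm after the tools are switched on.

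**Working it through.** The plan gives no recording-error rate, so it has no figure to reproduce. The check has two parts.

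**1. Does difference-in-differences remove the problem?** Write recorded coverage as R = C + e, where C is true coverage and e is the net recording error (cover recorded but not held, minus cover held but not recorded). Then

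DID(R) = DID(C) + [change in e at tool clinics - change in e at control clinics].

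- If e differs between groups but stays constant over time, the bracket is zero.
- If e changes equally in both groups, the bracket is zero.
- If e changes at go-live at tool clinics only, the bracket is not zero and has the same form as a treatment effect. Random effects for clinic and serial correlation, and patient covariates, do not separate the two.

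The same holds for Arm II against Arm I if tool use differs. Past validation of EHR data bears on the level of e, not on whether its change stays equal between groups once the tools are on.

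**2. How large could it be?** Inputs from Table 1 (OCHIN, 2014): 34.0% with no insurance; 17.6% private + 48.4% public = 66.0% insured. All other rates are assumptions, and extra correction at control clinics is set to zero.

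*Upward:* spurious effect = 34.0% x share of these who in fact hold cover x share corrected.

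| Share holding cover | Share corrected | Spurious effect (points) |
|---|---|---|
| 2% | 25% | 0.34 x 0.02 x 0.25 = +0.17 |
| 5% | 50% | 0.34 x 0.05 x 0.50 = +0.85 |
| 10% | 100% | 0.34 x 0.10 x 1.00 = +3.4 |
| 20% | 100% | 0.34 x 0.20 x 1.00 = +6.8 |

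*Downward:* spurious effect = -(66.0% x share of these whose cover has lapsed x share corrected).

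| Share lapsed | Share corrected | Spurious effect (points) |
|---|---|---|
| 2% | 25% | -(0.66 x 0.02 x 0.25) = -0.33 |
| 5% | 50% | -(0.66 x 0.05 x 0.50) = -1.65 |
| 10% | 100% | -(0.66 x 0.10 x 1.00) = -6.6 |

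Three limits apply. Table 1 counts patients across all of OCHIN, whereas the exposed outcome is scored at visits in selected clinics. The downward rows apply correction to everyone recorded as insured, although the registries list only those who may be near expiry, so their upper end is generous. Control staff also handle insurance data for billing, so some correction occurs there too, which would shrink either figure.

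**The case against.** The strongest reply has four parts.

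- **The mechanism is inferred.** The added data elements are not named or tied to an outcome. The alerts and registries are described as serving outreach, enrollment and re-enrollment. No sentence says that they ask staff to verify or correct recorded coverage. This stands, and the point must be conditional.
- **An external source is already planned.** The abstract names Medicaid data, and the continuity outcome is specific to Medicaid, so that outcome may already be meant to come from Medicaid files. An article may leave the source of each outcome to the full protocol. This stands for continuity. It leaves visit coverage exposed, because the Methods name the EHR as the source of insurance dates and types.
- **The EHR statement sits under the pre-implementation phase.** It covers baseline and policy analyses and does not say that post-implementation outcomes come from the EHR alone. That is correct as a reading, but a pre/post comparison needs the same measure in both periods.
- **The direction is open.** A reader might infer that the tools prompt staff to record insurance and that better recording will therefore look like a coverage gain. The documents do not support that certainty. Correcting a record of no insurance raises recorded coverage, but checking patients near expiry can reveal lapses and lower it. One may argue that upward bias is likelier because the registries target the uninsured; the text does not settle this.

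**Conclusion.** The point holds as a conditional risk to one outcome: coverage at visits, and the Reach measure built on it, where these are taken from the EHR. If the tools change how coverage is checked or recorded, the bias starts at go-live, may go either way, and survives difference-in-differences. No section of the article addresses it.

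Its size is unknown. The spread of about +6.8 to -6.6 points is an illustration that rests on assumed error and correction rates and on no extra correction at control clinics. It is not an estimate.

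Two stronger conclusions should not be drawn. The risk does not extend to every insurance outcome, because Medicaid continuity can come from Medicaid data. Nor may a gain seen only in the EHR be dismissed as a recording effect: Medicaid files cannot show private cover (17.6% of OCHIN patients in Table 1) or confirm true gains in patients who do not link. This is a cheap improvement, not a defect that invalidates the design.

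**What to change.** In the Pre-implementation phase section and the quantitative analysis of the effectiveness component:

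1. Take the Medicaid continuity outcome from the Medicaid data named in the abstract, for intervention and control clinics and for both periods, wherever those data are held.
2. Build EHR visit coverage only from payer and coverage fields in use at all clinics before go-live. Exclude data elements added by the tools.
3. Among linked patients, report EHR-Medicaid agreement by group (Arm I, Arm II, control) and period.
4. As a sensitivity analysis, repeat the visit-coverage difference-in-differences with Medicaid enrollment as the reference for Medicaid cover.
5. If agreement shifts differently by group, interpret an EHR-only change with caution, without automatically calling it recording.

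The cost is some wording, linkage to a source already named, and one extra table and analysis. The downsides are that Medicaid files may lag, may not be held for all three states, and will not link for some patients.

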### Effectiveness-implementation hybrid study design

To further study the uptake and use of these health insurance support technologies, we will blend design components of clinical effectiveness and implementation research. Using an “effectiveness-implementation hybrid design,” as described by Curran and collaborators [32], this intervention study will simultaneously assess the effectiveness of (i) health insurance support HIT tools and (ii) the best strategies for implementing the tools in CHCs. We hypothesize that patients seen at CHCs that receive these insurance support HIT tools will have higher rates of continuous insurance coverage and will be more up-to-date on age- and gender-appropriate cancer screening and prevention services, as compared to those seen at CHCs without the tools. We further hypothesize that CHCs that receive enhanced training and facilitation to support tool use will have higher rates of uptake of the tools and better insurance and cancer prevention rates than CHCs that receive the tools without such enhanced training or those without the tools.

Specifically, we will assess the effectiveness and implementation of a suite of health insurance support HIT tools designed to (1) identify and assist in contacting uninsured CHC patients who are eligible for enrollment in Medicaid and (2) encourage re-enrollment of Medicaid-insured patients before coverage gaps occur. The current study builds on our preliminary work by refining and studying the effectiveness of EHR-based health insurance support HIT tools across a larger number of clinics and studying effective methods for implementation of such tools in an adult patient population [30, 33–35].

### Study objectives

Assess the effect of the health insurance support HIT tools on patients’ health insurance coverage rates.Assess the effect of the health insurance support HIT tools on up-to-date status of cancer screening and preventive care received by patients.Compare two levels of implementation support, evaluating patient and CHC staff acceptance and use of the health insurance support HIT tools, and patient-, provider-, and system-level factors associated with successful implementation of the tools.

## Methods/design

### Trial design

This is a two-arm, cluster-randomized trial with an external matched control group of clinics, which utilizes a hybrid design: an effectiveness and implementation trial [32, 36–38]. To test for *implementing the tools*, intervention clinics will be randomized to one of the two implementation support arms (see Fig. 1). Thus, all intervention clinics will receive the health insurance support HIT tools but will be randomly assigned to Arm I (tool + basic training) or Arm II (tools + enhanced training + facilitation) as depicted in Fig. 1. The *implementation* component of the trial will evaluate the relative impact of the different support strategies in Arm II. For the *effectiveness* component of the trial, we will compare the intervention group (all participating clinics) to a propensity score-matched [39–41] group of control clinics to assess the extent to which the use of insurance support HIT tools facilitates continuous health insurance coverage and improved cancer prevention care.

**Fig. 1 Fig1:**
[figure not shown]
Effectiveness-implementation hybrid design

### Study setting and population

The study will be carried out at OCHIN, a non-profit 501(c)(3) collaborative that was created in 2001 to develop HIT tools for CHCs. Originally called the Oregon Community Health Information Network, OCHIN has 81 health system members in 17 states with 376 clinics and 6322 providers caring for nearly 2,000,000 patients.

OCHIN provides and maintains a comprehensive electronic health information infrastructure, built on software from Epic© Systems. The OCHIN EHR is linked across all member clinics through an Organized Health Care Arrangement, which gives clinics a fully integrated EHR in which each patient has a single medical record. There is one enterprise-wide master patient index; health record data “follow the patient” to any OCHIN clinic.

The Institutional Review Board of the Oregon Health & Science University has reviewed and approved this study. The study is registered with ClinicalTrials.gov (#NCT02355262).

*Inclusion criteria for intervention and control sites*. Study sites were required to be primary care clinics that implemented the OCHIN EHR prior to January 1, 2013, have >1000 adult patients with ≥1 visits in the past year, and be located in a state that expanded Medicaid in 2014 [42].

*Inclusion criteria for patients*. All patients (ages 18–64) with at least one encounter at a CHC in OCHIN since January 1, 2013 (*n* ≈ 1,000,000 adults), will be included in the study dataset for quantitative analysis. As very different insurance products are available to children <18 and patients >64 years of age, these age groups are excluded. All study sites serve low-income, ethnically diverse populations with lower rates of cancer screening (see Table 1) and higher rates of publicly insured and uninsured patients, compared to national rates [43].

**Table 1 Tab1:** Insurance coverage and cancer screening rates in the US population and OCHIN

	US population, 2010 (%)	OCHIN, 2014 (%)
Insurance coverage		
Private	64.2	17.6
Public	34.3	48.4
None	13.4	34.0
Cancer screening among insured patients		
Cervical	83.0	36.5
Colorectal	58.6	42.8
Breast	72.4	60.3
Cancer screening among uninsured patients		
Cervical	63.8	27.0
Colorectal	20.7	19.9
Breast	38.2	39.3

Source for US population: Census [71], CDC [72]; source for OCHIN population: OCHIN EHR data

